**Methods:**

Participants with stroke who demonstrate the ability to grasp and lift cubic wood blocks of different sizes (2.5cm^3^, 5cm^3^, and 10cm^3^) using their affected hand will be divided into three groups: A, B, and C. Each group will consist of twenty stroke patients, resulting in a total of sixty participants with stroke. Additionally, twenty matched healthy subjects will be enrolled as a control group. Comprehensive assessments will be conducted before and after the intervention, including blood oxygen parameter monitoring of the cerebral cortex and upper limb flexors using fNIRS during the grasping task. Other assessments will include MyotonPRO, the Modified Ashworth Scale, the upper extremity section of the Fugl–Meyer Assessment, the Action Research Arm Test, and the Modified Barthel Index. The study will be undertaken between January 2024 and September 2025.

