## Methods and design

### Study design

This study follows a longitudinal non-randomized controlled design to examine the synchronous oxygenation characteristics of the central cortex and upper-limb flexors during a grasping task in stroke patients with varying levels of grasp function.

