### Participants

Inclusion Criteria:

1.First stroke confirmed by CT or MRI.2.Medically stable.3.Age between 40 and 80 years.4.Onset of stroke occurred between two weeks to three months.5.Right handedness.6.No severe cognitive impairment (MMSE ≥ 22 points) and able to follow motor commands.7.Able to maintain an upright position in an armless seat for at least 30 min.8.Modified Ashworth grade of the affected upper limb is equal to or less than grade 2.9.Brunnstrom motor function grade of the affected hand is equal to or greater than grade 3, and able to grasp a 2.5cm3 wood block with effort.10.Patient and their family members agree to participate in the study and have signed the informed consent.

Exclusion Criteria:

1.Unstable clinical condition.2.Presence of any neuropsychiatric illness other than stroke.3.Diagnosis of schizophrenia, bipolar disorder, obsessive-compulsive disorder, personality disorder, or major depression.4.Presence of skin lesions or infections on the upper limb.5.History of upper limb fractures, deformities, or finger absence.

Sample Size:

Based on the sample size of previous studies (Huo et al., 2019a), a total of 60 patients following stroke will be enrolled in this study, with 20 patients in each of the three groups.

Group A: Patients who can only grasp and lift a 2.5 cm^3^ wooden block with their hemiplegic hand.Group B: Patients who can grasp and lift 2.5 cm^3^ and 5 cm^3^ blocks with their hemiplegic hand but cannot lift 10 cm^3^ blocks.Group C: Patients who can pick up 2.5 cm^3^, 5 cm^3^, and 10 cm^3^ wood blocks with their hemiplegic hand but exhibit abnormalities in speed and coordination during the task.

In addition, a control group of 20 age-matched healthy subjects without neurological diseases or history of upper limb trauma will also be enrolled.

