### Statistical analysis

Before conducting parametric tests, several steps were taken to prepare and analyze the data. Outliers were identified using normal Q–Q plots and box plots, and data points that were more than three standard deviations from the mean were considered outliers and subsequently excluded from the analysis (Minati et al., 2011). Missing values were addressed using multiple imputation analysis to estimate and replace the missing data points (Blankers et al., 2010).

Descriptive statistics were used to summarize the demographic and clinical characteristics of the study participants. The normality of the data distribution was assessed using the one-sample Kolmogorov-Smirnov test. For comparisons between different groups, chi-square tests were used for categorical variables, while independent t-tests were used for continuous variables.

To evaluate the differences in outcome measures before and after the intervention for participants with stroke, paired sample *t*-tests were employed. The correlations between variables were assessed using either the Pearson correlation coefficient (r) or the Spearman correlation coefficient (ρ), depending on the nature of the data.

The significance of interregional coupling strength between the resting state and different grasping states was evaluated using a one-way analysis of variance (ANOVA). Additionally, χ^2^ tests were utilized to identify statistically significant differences in interregional coupling direction between the resting state and different grasping states.

All statistical analyses were performed using SPSS software (version 20.0; SPSS Inc., Chicago, IL, USA). All tests were two-tailed, and a significance level of *p* < 0.05 was considered statistically significant.

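### Controls are matched on age, but the stated between-group t-test ignores age, so patient-control and A/B/C contrasts may carry an age difference and may lose precision

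*Protocol article*

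**What the plan says.** **Design.** Study design states: "This study follows a longitudinal non-randomized controlled design". Under Participants, groups A, B and C are formed by the largest block the patient can lift with the affected hand, and "a total of 60 patients following stroke will be enrolled in this study, with 20 patients in each of the three groups". The eligible range for patients is "Age between 40 and 80 years"; nothing balances age across the three groups.

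**Controls.** Participants adds that "a control group of 20 age-matched healthy subjects without neurological diseases or history of upper limb trauma will also be enrolled". The abstract says only that "twenty matched healthy subjects will be enrolled as a control group", without naming the factor. Neither place says whether matching is individual or by frequency, or whether the reference is all 60 patients or one of the groups.

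**Analysis.** Statistical analysis gives one rule for comparing groups: "chi-square tests were used for categorical variables, while independent t-tests were used for continuous variables". Before-after changes in patients get paired t-tests. Coupling strength at rest and in the grasping states gets one-way ANOVA. No listed outcome analysis contains age or uses the matching.

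**Size.** The number of patients is set "Based on the sample size of previous studies". No effect size, standard deviation or power is given.

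**The concern.** A design that matches on age treats age as related to the outcome. The stated test then discards that factor. Two things can follow.

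1. If the groups have similar ages, the part of the outcome variance explained by age stays in the error term, and power is lower than it need be.
2. If the groups differ systematically in age, part of what is reported as an effect of stroke or of grasp level is an effect of age. Here the groups are formed by function and not by randomization, so such a difference is possible.

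The contrasts exposed are those behind the primary objective and the hypotheses in the Discussion: patients against controls, and A, B and C against each other, on cortical and muscle oxygenation. The Limitations section treats the non-randomized design as a limit on generalizability and does not mention differences between groups.

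**Working it through.** **Inputs from the document:** 20 per group (3 x 20 = 60 patients, plus 20 controls = 80), two-sided 5% level, independent t-test. There is no stated power figure to reproduce.

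**Assumptions (not in the document):** rho, the within-group correlation of age with the outcome, at 0.1, 0.3 and 0.5; a true difference of 0.8 SD; an age gap in SD units (with an age SD of 10 years, 0.5 SD is 5 years).

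**Step 1. Precision when ages balance.**
Unadjusted: noncentrality = d x sqrt(n1 n2/(n1+n2)) = 0.8 x sqrt(400/40) = 2.53, with 38 df. Power is 69.3%.
With age as a covariate, the residual variance is multiplied by (1 - rho²), so d becomes d/sqrt(1 - rho²), with 37 df. At rho 0.3 this is 0.8/sqrt(0.91) = 0.839. The loss in patients per group from leaving age out is 20/(1 - rho²) - 20.

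| rho | Power at 0.8 SD | Difference detectable with 80% power | Patients per group lost |
|---|---|---|---|
| age ignored | 69.3% | 0.909 SD | - |
| 0.1 | 69.7% | 0.905 SD | 0.2 |
| 0.3 | 73.3% | 0.868 SD | 2.0 |
| 0.5 | 81.2% | 0.788 SD | 6.7 |

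**Step 2. Systematic age difference.**
False difference = rho x gap. For a gap of 0.5 SD this is 0.3 x 0.5 = 0.15 SD or 0.5 x 0.5 = 0.25 SD. The rejection rate of the nominal 5% test, with no true group effect, comes from the noncentral t at that shift:

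| Age gap | rho 0.1 | rho 0.3 | rho 0.5 |
|---|---|---|---|
| 0.25 SD | 5.1% | 5.6% | 6.7% |
| 0.5 SD | 5.3% | 7.5% | 12.0% |
| 1.0 SD | 6.1% | 15.2% | 33.8% |

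**Step 3. Why matching to the pooled patients does not settle it.**
Suppose, as an illustration, that the mean ages of A, B and C were 5 years apart with SD 10, and controls were centred on the pooled mean. The gaps to controls would then be -0.5, 0 and +0.5 SD, and A and C would differ by 1.0 SD, although matching to the pooled mean had succeeded.

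**Step 4. Individual matching.**
If each control were matched to one patient, exact age matching would give a pair correlation of rho²: 0.09 at rho 0.3 and 0.25 at rho 0.5. In 40,000 simulated trials the unpaired t-test at nominal 5% rejected 4.1% and 2.5% of the time. In that case the error runs the other way and the test is conservative.

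**The case against.** **The controls can fit all three groups.** A reader might infer that 20 controls cannot be matched to A, B and C at once. The document does not support that. If the three groups have similar age distributions, one control set fits them all, and the document states no relation between age and grasp level. What stands is narrower: the reference for matching is not stated, and balance with each group is not guaranteed.

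**Chance imbalance is harmless to the error rate.** With age SD 10 and identical underlying ages, the means of three groups of 20 would span 5 years or more in about 25% of trials. It is tempting to read this as an inflated error rate. It is not: chance gaps are already in the standard error, and the t-test keeps its 5% over repeated trials. The rates in Step 2 need a systematic difference, for which the document gives no direct evidence.

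**The effect may be trivial.** At rho 0.1 the power gain is 0.4 points, and even a 1 SD age gap gives only 6.1%. This stands; matching on age does not show that rho is large.

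**The quoted sentence may concern baseline tables only.** It follows the sentence on demographic description. On that reading age would be compared between groups, but the patient-control and A/B/C outcome contrasts would have no stated test. Comparing age at baseline also does not put age into an outcome analysis.

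**A fuller analysis plan may add age.** It may. The article nevertheless names a specific unadjusted test, and the point addresses that choice.

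**Conclusion.** The point holds for between-group contrasts only. The design matches on age, the groups are not randomized, and the one stated test for continuous outcomes between groups leaves age out. The contrasts may carry an age difference and may lose precision; the document does not show that they do.

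The before-after paired tests and the rest-against-grasp comparisons are within-person, so age does not bias them and the secondary objective is not touched in that respect.

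The size is conditional on assumed values: a power gain of 0.4 to 11.9 points (69.3% to 69.7% or 81.2%) for rho from 0.1 to 0.5 at a difference of 0.8 SD, and a rejection rate of 5.3% to 12.0% for a systematic gap of 0.5 SD over the same range. The unadjusted test is not invalid in itself, and with individually matched controls it would err on the cautious side. The case for change is that the remedy is specific and nearly free, not that the damage is proven.

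**What to change.** 1. For each block-size condition, analyse between-group continuous outcomes with a linear model of outcome on group plus age in years, and report age-adjusted contrasts. Include only the groups that perform that condition. According to the fNIRS data acquisition section these are A, B, C and controls for the smallest block; B, C and controls for the middle one; C and controls for the largest. One four-group model for all conditions would not fit this design.
2. Keep the unadjusted t-test as a sensitivity analysis.
3. State whether matching is individual or by frequency, and whether its reference is the pooled 60 patients or a particular group. If it is individual, the analysis should also respect the pairs.

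**Cost.** A few sentences and one degree of freedom per model: with complete data, error df of 80 - 4 - 1 = 75, 60 - 3 - 1 = 56 and 40 - 2 - 1 = 37 for the three conditions. Age is already needed for patient eligibility and for matching, and SPSS fits the model. The price is reliance on a roughly linear age effect, which can be checked with a residual plot.

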#### fNIRS system and data analysis of cerebral cortex

In this study, the NirSmart-6000A equipment (Danyang Huichuang Medical equipment Co., Ltd, China) was used to continuously measure and record changes in the concentration of HbO and HbR in the cerebral cortex during the grasping task. The system consisted of near-infrared light sources (LEDs) and avalanche photodiodes (APDs) as detectors. The wavelengths used were 730 nm and 850 nm for the LED and APD, respectively, and the sampling rate was 11 Hz. Fourteen light sources and fourteen detectors were used, forming a total of 35 effective channels (CHs) as shown in Figure 4. The average distance between the light sources and detectors was 3 cm, ranging from 2.7 cm to 3.3 cm. To define the coordinates of the acquired channels, an NIRS-EEG compatible cap from EASYCAP, Herrsching, Germany, based on the international 10/20 system, was used for localization. The brain regions observed in this study were the bilateral prefrontal cortex (LPFC/RPFC), motor cortex (LMC/RMC), and occipital lobe (LOL/ROL), according to existing literature. No detector signal supersaturation occurred during the recording process. The middle point of each channel was defined as the main brain region detected by that channel, and the coordinates of each channel were calibrated using this point as the center of a circle. The Montreal Neurological Institute (MNI) coordinates of each channel were calculated and registered based on the 10-20 system using the NIRSpark (Danyang Huichuang Medical equipment Co., Ltd, China). The corresponding brain regions were then identified in the adult Brodmann Chris Rorden’s MRIcro brain model. The coordinates of each channel and the calibration information of the brain regions are provided in Table 1.

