CH31	S12	D13	20.445	−2.6141	76.598	6−Pre-Motor and Supplementary Motor Cortex	1
CH32	S13	D11	−34.819	−22.105	73.515	4−Primary Motor Cortex	0.6528
CH33	S13	D14	−23.263	−20.709	77.36	4−Primary Motor Cortex 6−Pre-Motor and Supplementary Motor Cortex	0.4542 0.5458
CH34	S14	D11	−30.534	−1.1513	68.7	6−Pre-Motor and Supplementary Motor Cortex	1
CH35	S14	D14	−19.211	−0.49547	76.226	6−Pre-Motor and Supplementary Motor Cortex	1

Some channels may cover more than one brain region. To save space in this paper, only the brain regions with a coincidence degree higher than 0.4 are listed in this table.

For data analysis, the NirSpark software package, running in MATLAB (The Mathworks, USA), was utilized. The data preprocessing involved several steps, including eliminating irrelevant time intervals, removing non-related artifacts, converting light intensity to optical density, applying a band-pass filter, converting optical density to blood oxygen concentration, and setting parameters for the hemodynamic response function (HRF). The HRF initial time was set to −2 s, and the end time was set to 40 s, with a baseline state from −2 s to 0 s and a single block paradigm from 0 s to 40 s. Both the “start” and “rest” durations were set to 20 s. The blood oxygen concentration data from the three block paradigms were then averaged to generate a block average result. These preprocessing steps allowed for meaningful analysis of the fNIRS data, providing insights into changes in cerebral blood flow and oxygenation during the experimental conditions.

In this study, the Generalized Linear Model (GLM) (Uga et al., 2014) was utilized to analyze the pre-processed time-series data of HbO for each channel and subject. A t-test was performed (P < 0.05) to compare the baseline and task states. The GLM allowed for the establishment of an ideal Hemodynamic Response Function (HRF) specific to each task and subject. The similarity between the experimental and ideal HRF values was evaluated (Chung et al., 2018). The beta value, representing the level of cortical activation for each channel, was used as an estimate of the HRF prediction for the HbO signal (Kawabata et al., 2019). It indicates the peak value of the HRF function and serves as a measure of cortical activation.

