### Outcomes

#### Primary outcomes

In this study, two different applications of functional near-infrared spectroscopy (fNIRS) were employed: fNIRS of the cerebral cortex and fNIRS of the upper-limb flexors.

For fNIRS of the cerebral cortex, a Huichuang portable 35-channel fNIRS system was utilized to measure blood oxygen parameters, including HbO, HbR, and HbT. The system used the continuous wavelet transform method to calculate the wavelet amplitude (WA) of signals ranging from 0.01 to 0.08 Hz in each cortical region (Huo et al., 2019a). The phase information was extracted from the signals. The inter-hemispheric lateral degeneration index was then calculated based on WA to evaluate the degree of brain activation transfer from the affected side to the healthy side. Additionally, the extracted phase information was used for effect connection analysis based on dynamic Bayesian inference to assess the strength of the interaction between the cerebral cortex regions (Huo et al., 2019a).

For fNIRS of the upper-limb flexors, a portable muscle oxygen detector called OctaMon from Artinis Medical Systems B. V. was employed. This system utilized an 8-channel near-infrared spectroscopy setup to measure blood oxygen parameters (HbO, HbR, HbT) in the flexor muscles of the upper limb. A distribution map was created based on the measured parameters. The spatial-temporal parameters of blood oxygen were analyzed to evaluate muscle activities.

Overall, both fNIRS applications aimed to investigate blood oxygen parameters in different regions of interest (cerebral cortex and upper-limb flexors) and analyze their characteristics to understand brain activation transfer, cerebral cortex interactions, and muscle activities in the context of the study.

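### Two-sample t-tests are named for a four-group design, and 35 cortical channels are each tested at an unadjusted 0.05, so false positives exceed the stated 5%

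*Protocol article*

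**What the plan says.** Under Participants, the protocol article plans three stroke groups defined by grasp ability, "with 20 patients in each of the three groups", and "a control group of 20 age-matched healthy subjects". That makes four groups.

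Under Statistical analysis, categorical variables are compared between groups by chi-square tests, while "independent t-tests were used for continuous variables". One-way ANOVA appears in the same section, but only for coupling strength between resting and grasping states. The section closes with "All tests were two-tailed, and a significance level of" p < 0.05.

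Under the heading on the fNIRS system and data analysis of cerebral cortex, 35 channels are described. A GLM "was utilized to analyze the pre-processed time-series data of HbO for each channel and subject", and then: "A t-test was performed (P < 0.05) to compare the baseline and task states". No correction across channels is given there or elsewhere in the article. The Primary outcomes section names several cortical and muscle measures without ranking them; the cortical system is to "measure blood oxygen parameters, including HbO, HbR, and HbT".

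**The concern.** An independent t-test compares two groups. Applied to four, it becomes a set of pairwise tests, each at 0.05, with no overall test to guard them. The channel analysis has the same weakness on a larger scale: 35 tests per condition, each allowed its own 5% error.

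The primary objective is to characterise cortical and muscle oxygenation during grasping, so the list of channels called active and of groups called different is itself the result. If the stated threshold is applied as written, some entries on that list will be noise, and a reader cannot tell which.

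**Working it through.** **Figure to reproduce.** The article gives only the sample size, 3 × 20 = 60 patients plus 20 controls, taken from previous studies. It states no power, effect size or familywise error rate, so there is no error figure to reproduce.

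**Inputs.**
- Groups: four, 20 each (Participants).
- Who grasps which block (fNIRS data acquisition and analysis): A the 2.5 block only; B the 2.5 and 5; C and controls all three.
- Cortical channels: 35. Threshold: 0.05, two-sided, for every test.
- Correlation between channels: not given; assumed from 0 to 0.9.

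**Step 1: group comparisons on one outcome, no true difference.** The number of pairs among g groups is g(g − 1)/2. Treating pairs as independent gives 1 − 0.95^k, which is too high because pairs share groups. The simulated column uses 100,000 null data sets, normal outcomes, 20 per group and pooled t-tests on 38 degrees of freedom.

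| Measured in | Pairs k | 1 − 0.95^k | Simulated |
|---|---|---|---|
| Four groups (2.5 block, or any measure taken in all groups) | 6 | 0.265 | 0.204 |
| Three groups (5 block: B, C, controls) | 3 | 0.143 | 0.123 |
| Two groups (10 block: C, controls) | 1 | 0.05 | nominal |

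One-way ANOVA across the four groups in the same simulated data rejects at a rate of 0.050. The clinical scales are described for stroke participants; where only A, B and C have a measure, the three-group row applies.

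**Step 2: channel tests in one condition, no channel active.** Expected false activations are 35 × 0.05 = 1.75, whatever the correlation. With independent channels, the chance of at least one is 1 − 0.95^35 = 1 − 0.166 = 0.834. With equal correlation rho between channels, 10,000 simulated data sets (a one-sample t-test over 20 participants per channel) give:

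| Assumed rho | 0.3 | 0.5 | 0.7 | 0.9 |
|---|---|---|---|---|
| P(at least one false activation) | 0.73 | 0.56 | 0.38 | 0.19 |

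**Step 3: allow for true activation.** Table 1 of the article places 16 of the 35 channels (CH1-2, CH13-18, CH28-35) over primary motor, premotor/supplementary motor or primary somatosensory cortex. If all 16 are truly active, 35 − 16 = 19 can give false positives. The expected number is 19 × 0.05 = 0.95, and the chance of at least one under independence is 1 − 0.95^19 = 0.62.

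**The case against.** The strongest replies are these.

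- **Multiplicity is often left to the analysis plan.** That plan is not shown, and silence in a condensed article would not be a finding. This stands as far as it goes, but the article is not silent: it names a two-group test and sets 0.05 for all tests. A plan that corrects for multiplicity would have to override this text.
- **The t-test sentence may concern only baseline characteristics.** It follows the sentence on demographic and clinical description, and the article never says that all pairs will be tested. That makes 20% the figure for the case where all six contrasts are run. Even so, a two-sample test does not fit four groups.
- **Much of the analysis is not on 35 channels.** Wavelet amplitude is averaged by region and the lateralization index uses those averages. The stated channel test covers HbO only. No channel-by-channel test is stated for group contrasts or for the eight muscle channels. All of this stands and limits the point.
- **The study is small and its aims are largely exploratory**, and the Limitations section admits this. That lowers the stakes but does not make 0.05 the true error rate.

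A reader might go further and infer that false activations and false group differences are near certain. Counting 18 group-by-condition maps at baseline (2 + 4 + 6 + 6) and 12 after treatment (2 + 4 + 6) gives 30 × 35 = 1,050 tests and 1,050 × 0.05 = 52.5 expected false positives. The documents do not support this. The article describes a model for each channel and subject, not 30 maps. The count also assumes that no channel responds to grasping, which is implausible over the 16 sensorimotor channels. The 83% needs independent channels, although channels share sources and detectors, and a false group difference on one outcome has a chance of about 20%, not near 100%.

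**Conclusion.** The point holds in limited form. The named group test does not fit the four-group design, and the stated channel threshold does not hold error at 5% across 35 channels.

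For group comparisons, the error per outcome is about four times nominal where six contrasts are run (0.204 / 0.05), about two and a half times with three (0.123 / 0.05), and nominal with one. This assumes that every possible pair is tested and no true difference exists. For channels, even at an assumed correlation of 0.9, the 19% chance of at least one false activation per condition is nearly four times nominal. The 1.75 expected and the 83% are upper figures: both assume that no channel is active, and the 83% also assumes independence. The true correlation is unknown, and the channel figures treat the t-test as a group-level test on 20 participants. If it is run within each subject, there are more tests.

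**What to change.** Three changes to the analysis text, made before results are seen:

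1. Replace the independent t-tests with a one-way ANOVA or linear model on group, using only the groups that performed the given block, followed by Holm- or Tukey-adjusted pairwise contrasts. For the 10 block this reduces to a single comparison and needs no adjustment.
2. Apply Benjamini-Hochberg false discovery rate control at 5% across the 35 cortical channels within each condition, and across the muscle channels if they are tested singly.
3. Report results outside this control as exploratory. Control within a condition does not cover multiplicity across conditions and outcomes, so the text should say so.

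No new data, participants or design change are needed. The cost is fewer nominally significant channels and contrasts. As an upper bound on the loss for six contrasts, take Bonferroni at 0.05/6 = 0.0083, which Holm never does worse than. With 20 per group and the normal approximation, power for an assumed standardised difference of 0.8 falls from about 72% to 46%, and for 1.0 from about 89% to 70%. For channels, the strictest Benjamini-Hochberg step is 0.05/35 = 0.0014, and later steps are less strict.

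### The only between-group test named for continuous variables is the two-sample t-test, unadjusted, although some comparisons involve three or four groups; if all pairs are tested, the false-positive risk is about 12% or 20%

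*Protocol article*

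**What the plan says.** The Study design section describes a non-randomised controlled study of oxygenation during grasping "in stroke patients with varying levels of grasp function". The Participants section defines groups A, B and C by the largest block the patient can lift, "with 20 patients in each of the three groups", and adds "a control group of 20 age-matched healthy subjects without neurological diseases". That makes four groups of 20.

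The Statistical analysis section gives one sentence on group comparisons: "For comparisons between different groups, chi-square tests were used for categorical variables, while independent t-tests were used for continuous variables". The part at issue is that "independent t-tests were used for continuous variables". The section closes with: "All tests were two-tailed, and a significance level of *p* < 0.05 was considered statistically significant". The other methods in that section do different jobs. Paired t-tests cover change from before to after the intervention in stroke participants, and correlation coefficients relate variables to each other. One-way ANOVA is used for coupling strength at rest against the grasping states. The section states no overall test across groups and no adjustment for several group comparisons.

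The section on fNIRS data acquisition shows which groups do which task. Group A grasps only the 2.5 cm³ block, B the 2.5 and 5 cm³ blocks, and C and the healthy controls all three. The Experimental procedure section describes the clinical scales for stroke participants.

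**The concern.** An independent t-test handles two groups. With three or four, it can only be applied pair by pair, or after merging groups in a way the article does not describe. Pairwise testing with each test at 0.05 raises the chance of declaring some group difference when none exists, and this happens within a single outcome. Naming one lead outcome would not remove it.

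The group comparison is central to the study. The primary objective and the design statement concern how oxygenation looks across grasp levels and against healthy subjects. A reader of the results could not tell a real difference between two groups from the best of several unprotected tests.

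**Working it through.** The plan has no figure of its own to reproduce: it states no family-wise error rate, and the sample size is taken from a previous study without an effect size, SD or power.

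**Inputs from the article.** Group size n = 20; two-sided α = 0.05 for each test; two-sample t-test, df = 20 + 20 − 2 = 38.

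**Inputs assumed.** Normal data, equal SDs and equal true means, so that any significant result is false. All listed pairs are tested.

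**Step 1: count groups and pairs**, pairs = k(k − 1)/2.

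| Comparison | Groups | Pairs |
|---|---|---|
| 2.5 cm³ task | A, B, C, healthy (k = 4) | 4 × 3/2 = 6 |
| 5 cm³ task | B, C, healthy (k = 3) | 3 × 2/2 = 3 |
| Clinical scales | A, B, C (k = 3) | 3 |
| 10 cm³ task | C, healthy (k = 2) | 1 |

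**Step 2: upper reference.** If the tests were independent, the risk would be 1 − 0.95⁶ = 26.5% for six and 1 − 0.95³ = 14.3% for three. Pairs share groups, so the tests are correlated and the true figures are lower.

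**Step 3: allow for the correlation.** In 400,000 simulated trials with groups of 20, I counted those with at least one |t| above the 38-df critical value. The large-sample check is the probability that a studentized range over k groups exceeds 1.96 × √2.

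| Tests made | Simulation | Studentized range |
|---|---|---|
| All 6 pairs, four groups | 20.4% | 20.3% |
| All 3 pairs, three groups | 12.2% | 12.2% |
| A, B and C each against healthy | 12.6% | not applicable |
| C against healthy only | 5%, by construction | not applicable |

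**Step 4: the same null with a test that fits.** With four groups of 20, the one-way ANOVA F test (3 and 76 df) rejects in 5.0% of trials.

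**Step 5: the price for single pairs.** Tukey for four groups has a critical t of 2.63 on 76 df, a nominal p of about 0.010. Dunnett for three groups against healthy needs about 0.019.

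**Step 6: does using the order of the groups help?** Only under assumed patterns of means, since the article gives none:

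| Assumed means | Trend contrast (−3, −1, 1, 3) | F test |
|---|---|---|
| Equal steps of 0.20 SD | 51% | 34% |
| Equal steps of 0.25 SD | 70% | 51% |
| Equal steps of 0.30 SD | 84% | 69% |
| A = B = C, healthy differs by 0.75 SD | 60% | about 65% |
| B and C raised 0.75 SD above A and healthy | 5% | 79% |

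The trend contrast gains when means rise steadily and loses otherwise, in the last row almost completely.

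**The case against.** The strongest objection is about scope. The t-test sentence sits in the paragraph on demographic and clinical characteristics, and outcome analyses start in the next paragraph. On that reading it covers baseline description, and a condensed article may leave the outcome comparison to the full plan. The ambiguity is real, but it does not rescue the sentence. Baseline comparisons also involve three or four groups, and the section offers no other test between groups.

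Second, the article lists no pairs. The hypotheses in the Discussion contrast stroke with healthy, and one t-test of 60 against 20 would answer those at 5%. This stands as a limit on the figures, which hold if all pairs (or all three stroke-versus-healthy pairs) are tested. It does not cover comparisons among A, B and C, for which the design formed the groups.

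Three stronger readings are tempting, and the article does not support them.
- A reader might infer that every outcome carries a 20% risk. Only the 2.5 cm³ task brings four groups together. The lateralization index is defined by affected and unaffected hemisphere, so as written it gives no value for healthy subjects.
- A reader might infer that the plan commits to six tests per outcome. It does not say so.
- A reader might infer that ignoring the order of the groups is an error and that a trend test should lead. The article speaks of "stroke patients with varying levels of grasp function" but predicts no steady gradient, and does not place healthy subjects one equal step beyond C. A trend test is a possible gain in power, not a condition for validity.

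It is also fair to say that the fix will not make neighbouring groups easier to separate. At an assumed 0.25 SD per step, an unadjusted t-test of two neighbours has about 12% power, and Tukey about 4%.

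**Conclusion.** The point holds as a mismatch between a stated method and the design. The article names a two-sample test, unadjusted, as its only group comparison for continuous variables, while some comparisons involve three or four groups. If all pairs are tested, the chance of at least one false group difference is about 20% on the 2.5 cm³ task and about 12% on the 5 cm³ task and the clinical scales. Restricting the 2.5 cm³ task to each stroke group against healthy gives about 13%. The 10 cm³ task is correctly served by one t-test. These figures rest on normal data with equal SDs, 20 complete subjects per group and no true differences.

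The wording should be corrected before analysis: it bears on the main group comparison and is cheap to change.

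**What to change.** In the Statistical analysis section, replace the independent t-test for comparisons of three or more groups with a one-way ANOVA or a linear model with group as a factor, using the Welch version if variances differ (patients and healthy subjects may well differ in spread). Follow it with Tukey comparisons if all pairs matter, or Dunnett if the question is each stroke group against healthy, and state which. Keep the t-test for two-group comparisons such as C against healthy on the 10 cm³ block. State which groups enter each comparison, because this differs by task and by outcome.

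A linear trend contrast over A, B, C and healthy on the 2.5 cm³ task may be added as an optional secondary analysis. It pays off only if means change roughly monotonically with grasp ability.

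The cost is a few lines of text and no new data. The real downside is that a single pairwise difference needs a clearly smaller nominal p-value, about 0.01 instead of 0.05 with Tukey for four groups and about 0.019 with Dunnett, so power for any one pair falls.
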